### Study population

Between March 2023 and June 2024, children aged between 5–12 years old presenting to ED on one or more occasions or admitted to the general paediatric ward on one or more occasion in the last 12 months with asthma at selected study hospital sites within the three LHDs will be eligible to participate in the study. For those that fulfil all eligibility criteria (Box 1), each participant will be followed for a period of 12 months after enrolment. Informed written consent was sought from parents/carers of eligible children electronically via REDcap software.

Box 1Inclusion criteriaChildren aged between 5–12 years old.1 or more ED presentations or 1 or more hospital admission in the last 12 monthsChildren with current or history of physician-diagnosed asthmaChildren attended EDs or admitted to general paediatric wards with asthma exacerbation or asthma-related illnesses (e.g. wheeze) at hospitals within the three participating LHDs during the study periodParents/carers of non-English speaking background but understand English and do not require interpreter.Exclusion criteriaChildren with complex conditions e.g., genetic disorders, complex cardiac diseases etc.Children with high-risk and complex asthma who are already known to tertiary paediatric respiratory specialists.Children with significant developmental delays or comorbidities that will significantly limit their ability to participate in the study.Both parents/carers who do not understand English and require interpreterFamilies who do not have permanent housing e.g., live in a shelter.

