**Primary outcome **			
Health service use	• Hospital admissions • ED attendances • GP visits	Linked routinely collected medical records	Pre and post intervention

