**Secondary outcome **			
Asthma related quality of life in children	miniPAQLQ	Online questionnaire	Enrolment, 6 and 12 months
Asthma control	ACT or C-ACT	Online questionnaire	Enrolment, 6 and 12 months
Medication adherence	BMQ	Online questionnaire	Enrolment, 6 and 12 months
Patient and family reported experiences *Parental satisfaction* *travel*, *costs*, *missed school/work*, *asthma-self management knowledge *	Purpose designed questionnaire	Online questionnaire	Enrolment, 6 and 12 months

*Demographics*. Key demographic data including age, gender, language spoken at home, country of birth, parent/carer level of education, Socio-Economic Indexes for Areas (SEIFA) data and indigenous status will be collected from electronic medical records and the baseline questionnaire.

*Healthcare utilisation*. Researchers will focus on 3 key areas of healthcare utilisation: i) GP visits, ii) ED visits, and iii) hospital admission. This will be collected from electronic records and questionnaires.

*Asthma control*. Level of asthma control will be assessed using the Asthma Control Test (ACT; for children ≥ 12 years old) or Childhood Asthma Control Test (C-ACT; children 5–11 years old). These validated tools consist of 5–7 Likert-type scale questions, with a 4-week recall, assessing the frequency of shortness of breath and general asthma symptoms, use of rescue medication, the effect of asthma on daily functioning, and overall self-assessment of asthma symptom control. The total score range is 0–27 (C-ACT) and 0–25 (ACT) respectively, with a score on either test less than 19 indicating uncontrolled asthma [22].

*Quality of life*. Quality of life of the child will be assessed by using the miniPAQLQ validated tool [23], which consists of 13 questions in three domains (activity limitation, symptoms, and emotional function). The activity limitation domain includes 3 questions relating to play, sports and other daily activities; symptoms domain has 6 questions on cough, wheezing and nocturnal awakening; emotional function domain contains 4 questions associated with items such as being frightened, frustrated or feeling different, being irritable or worried, etc. Scores for each item range from 1 (maximum impairment) to 7 (no impairment). Overall score will be calculated by dividing the total scores with 13.

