#### School/Work absence

Parents/Carers will be asked at 6-month intervals to recall number of days their child has been absent from school/childcare or they have been absent from work due to their child’s asthma

*Sample size calculation*. Based on existing literature that shows 2.8% of paediatric ED attendances is asthma-related, we will be able to recruit at least 317 children from three LHDs for the impact assessment. Allowing for 15% attrition this will assure 270 participants for final analysis to detect a rate ratio of 2.6 in the mean number of asthma-related ED presentations before and after intervention, 80% power and 5% significance (two-sided). This calculation was based on the power calculation method for rate ratio of Poisson-distributed count data for a single sample setting.

Participants will be recruited from all eligible sites within each LHD. Recruitment of participants from each LHD will be proportional to the eligible catchment population within the specific LHD.

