Our trial has several limitations. First, the one-group pre-post-trial design limits our ability to assess and compare the effects of our initiative with usual care. However, the rationale for selecting this design is that the intervention involves providing a standardised asthma discharge package to eligible children, rendering the inclusion of a control waitlist impractical. After consultation with our LHD partners, a randomised controlled trial was deemed unsuitable due to the standardised nature of the intervention, thus making the proposed intervention essentially a part of standard care. We will collect and use self-reported participant data, which may introduce reporting bias. However, given the mixed-method methodology that will be employed, and the diversity of outcomes evaluated, the potential for reporting bias is minimal.

In conclusion, this study aims to significantly enhance access to asthma care, particularly targeting children in underserved communities like those living in rural and remote areas. By assessing implementation and economic factors, our research will provide comprehensive understanding of the effectiveness and viability of the model to help integrate it into standard practice. By utilising local resources, we can ensure the sustainability of improved healthcare services and help shed light on the potential for scaling up this model to benefit a wider population of children facing asthma-related challenges in underserved regions.

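### Reporting bias is called minimal for reasons that do not support it, and the article disagrees on whether questionnaire reports enter the primary utilisation counts

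*Protocol article*

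**What the plan says.** On self-report, the limitations part of the Discussion first concedes the problem: "We will collect and use self-reported participant data, which may introduce reporting bias". It then sets the problem aside, pointing to its mixed methods and its range of outcomes and concluding that "the potential for reporting bias is minimal". The same paragraph concedes that "the one-group pre-post-trial design limits our ability to assess and compare the effects of our initiative with usual care".

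On the source of the primary outcome (hospital admissions, ED attendances, GP visits), Aim 1 gives three descriptions:

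- Table 1, primary outcome row: "Linked routinely collected medical records".
- Data collection: electronic care records are the main source, both for the look-back of up to 5 years and at 12 months after enrolment.
- Healthcare utilisation paragraph, on the same three components: "This will be collected from electronic records and questionnaires".

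In Table 1 all four secondary outcome rows have an online questionnaire as their source, at enrolment, 6 and 12 months.

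**The concern.** Two things are at stake.

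First, a reader of the results will be told that the self-reported outcomes are almost free of reporting bias. If asthma control, quality of life, adherence and family experience improve after enrolment, the article offers no ground for separating real improvement from a change in how families answer.

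Second, if the Healthcare utilisation paragraph is followed as written, the primary counts may rest on a different mix of sources before and after enrolment. The planned interrupted time series estimates changes in intercept and slope at the intervention. A change in how completely events are captured, at or near that point, can appear as a change in level, which is one of the quantities being estimated. The same utilisation data also feed the economic evaluation.

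**Working it through.** **Does minimal follow from the reasons given?** Three features of the design bear on this.

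- Families know they are in the program. Under Study population, "Informed written consent was sought from parents/carers of eligible children electronically via REDcap software". They then receive the discharge package and text messages and, where asthma is uncontrolled, the offer of virtual home visits.
- There is one group, so a shift in reporting after enrolment has no concurrent arm in which to cancel out.
- The only check of a parent report against records described for Aim 1 is for oral corticosteroids. It is made where possible and is limited to hospital prescribing.

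Interviews and focus groups can help explain a questionnaire score but do not correct it. Several outcomes reported by the same informants can share the same bias. The conclusion does not follow.

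**Is ascertainment equal before and after?** The pre-period runs up to 5 years (60 months) and the post-period up to 12 months. Two questionnaires fall after enrolment and one falls at enrolment. No recall window for visits is stated. For other event-type items the stated window is six months: oral corticosteroid days in the preceding 6 months, and for absence, "Parents/Carers will be asked at 6-month intervals to recall number of days their child has been absent from school/childcare". The article does not say how questionnaire and record events would be combined.

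**Illustration.** The article has no figure of its own on this point to reproduce, so everything here is assumption. Let *u* be the share of extra events that questionnaires add in the months they cover, and *f* the fraction of the pre-period they cover. The post-period is taken as fully covered and the pre-period event rate as constant. Then

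observed post/pre ratio = true ratio × (1 + *u*) / (1 + *f* × *u*).

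With a six-month recall at enrolment, *f* = 6/60 = 0.1.

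| *u* | Multiplier, *f* = 0.1 | True 1.00 reads | True 0.80 reads |
|---|---|---|---|
| 0.10 | 1.10/1.01 = 1.09 | 1.09 | 0.87 |
| 0.20 | 1.20/1.02 = 1.18 | 1.18 | 0.94 |
| 0.30 | 1.30/1.03 = 1.26 | 1.26 | 1.01 |

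The limiting cases:

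- *f* = 0 (the enrolment questionnaire contributes nothing): a true 0.80 reads 0.80 × 1.10 = 0.88 to 0.80 × 1.30 = 1.04.
- *f* = 1 (the whole pre-period is recalled as completely as the post-period): the multiplier is 1 and there is no distortion.

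Pre-enrolment events that cluster close to enrolment would raise the effective *f* and shrink the distortion. Extra post-period events push the ratio up, so they tend to hide a reduction. The crude ratio only shows scale. In the article a rate ratio appears in the sample size calculation, while the planned analysis is the interrupted time series.

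**The case against.** The strongest reply is that the Data collection text governs the pre/post comparison and makes electronic records the main source in both periods. Table 1 agrees. The economic analysis takes encounter numbers from the health districts' own analysis units. ED visits and admissions are what hospital records should capture, so questionnaires may add little to them. The Discussion already admits possible reporting bias and the limits of a one-group design. How two sources are reconciled is something a condensed article may leave to a fuller document.

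Much of this stands. The text leans towards records, and for ED visits and admissions the exposure is probably small. It does not remove the point, for two reasons. The article does not merely omit a rule: it gives three different accounts of the source. And the sentence on reporting bias is a positive claim, not an omission.

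Three stronger readings are tempting, and the documents do not support them.

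- A reader might infer that questionnaire events are added after enrolment only. A questionnaire is also given at enrolment and could carry recall of earlier visits, so only unequal coverage is a fair inference.
- A reader might infer that the mixed sources would make the program look effective. Added post-period events work the other way. Favourable bias is the worry for the questionnaire scores, which is a separate matter.
- A reader might expect the oral corticosteroid check to measure the size of the bias. It covers hospital prescribing only, against parental recall of all days, so courses prescribed elsewhere would look like disagreement. It also says nothing about the control, quality of life or adherence scores.

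**Conclusion.** The point holds in two parts. The statement that reporting bias is minimal is not supported by the reasons given, and it matters most for the secondary outcomes, all of which are questionnaire reports from families aware of the program. Separately, the article contradicts itself on the source of the primary utilisation outcome, so equal ascertainment before and after enrolment is not assured.

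The size of the second part cannot be taken from the documents. Under the assumptions shown, a true ratio of 0.80 would read between 0.87 and 1.01. With fuller pre-period recall, or if few events are added, the effect shrinks towards nothing. GP visits are the component most likely to lean on questionnaires, though the article does not say so. This should be corrected before analysis. It does not by itself invalidate the record-based ED and admission results.

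**What to change.** 1. Align the Data collection text, Table 1 and the Healthcare utilisation paragraph so that each component has one named source. Count ED visits and admissions from the same record source in both periods, with no questionnaire-reported events added.
2. Keep GP visits in the primary outcome only if records cover both periods. Otherwise report them as a secondary, self-reported outcome.
3. Replace the sentence in the Discussion with a statement that self-reported outcomes are open to reporting and recall bias, and that conclusions on effectiveness rest mainly on record-based ED visits and admissions.

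The cost is wording and one source rule, with no new data collection. The downside is that GP visits may lose primary status.

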## List of abbreviations

AAIC: Aiming for Asthma Improvement in Children
AAP: Asthma Action Plan
ACT: Asthma Control Test
C-ACT: Childhood Asthma Control Test
CFIR: Consolidated Framework for Implementation Research
BMQ: Brief Medication Questionnaire
ED: Emergency Department
eMR: Electronic Medical Record
GEE: Generalized Estimating Equations
GP: General Practitioner
LHD: Local Health District
miniPAQLQ: Mini Paediatric Asthma Quality of Life Questionnaire
NSW: New South Wales
SCH: Sydney Children’s Hospital
SMS: Short Message Service
